**- Dependent variables:**

o Phantom limb pain: Short form McGill Pain Questionnaire. It is a scale that assesses pain from a quantitative and qualitative point of view. It consists of 15 pain descriptors, of which 11 are sensitive categories and 4 are affective. In addition, it contains an analog visual pain scale. It is self-answering and each descriptor has three columns (medium, moderate, severe), where the participant must mark the degree to which that descriptor persists in their pain. If you are not present, you can leave it blank. Columns are categorized as 0; no pain, 1; mig, 2; moderate, 3; severe. It takes between 2-5 minutes to be answered.

o Quality of life: EuroQol-5D-5L(15). It is a self-challenging scale consisting of 5 dimensions: mobility, self-care, regular activities, pain / discomfort and anxiety / depression. Each dimension has 5 levels: no problems, mild, moderate, severe and extreme problems. The participant is asked to indicate his / her state of health by ticking the box together with the most appropriate statement in each of the 5 dimensions. In addition, it contains a numerical scale from 0 to 100 to quantify the degree of health on the day of the assessment. It takes between 5-7 minutes to be answered.

o Functionality: Functional Independence Scale (FIM) (16). It is a scale built on 18 items within 6 areas of operation: personal care, sphincter control, mobility, gait, communication and social knowledge. The maximum score for each item is 7 and the minimum is 1. It takes 5 minutes to be answered.

o Psychological aspects: Beck depression inventory (17). It is a self-answering scale of 21 questions. Each question is quantified on a 4-point scale ranging from 0 to 3, with 0 experiencing no symptoms and 3 experiencing symptoms severely. It takes between 5-10min to be answered.

The following is a timetable detailing when each of the variables set out above will be collected.

| **Variable** | **Scale** | **Baseline** | **Post-intervention (9weeks)** | **Follow-up**  **(12 weeks post-intervention)** |
| --- | --- | --- | --- | --- |
| Socio-demographic |  |  |  |  |
| Amputation characteristics |  |  |  |  |
| Pain | SF-MPQ |  |  |  |
| Quality of life | EuroQol-5D-5L |  |  |  |
| Funcionality | FIM |  |  |  |
| Psychological aspects | Beck |  |  |  |

1. **STATISTICAL ANALYSIS:**

When performing a randomized cynical trial with mixed methodology we find two differentiated data analyzes.

Quantitative analysis:

The data obtained as study variables will be coded at the end of the collection, processed and analyzed by the members of the research group.

The population to be used as a sample in the analysis will include all participants who meet all the inclusion criteria, do not have any exclusion criteria and have given their consent to participate in the study. If a participant leaves before completing the study, he / she will not be replaced by another participant.

In the case of participants who have not completed the study due to dropout, have not fully completed treatment, or have even changed treatment, any data that may have been collected will be analyzed for intent to treat. The minimum number of sessions to be considered for the results will be 80%.

The program to be used for statistical analysis will be the SPSS5 program. A confidence level of 95%, and / or a statistical significance p <0.05 will be considered.

If a deviation from the intended method is considered necessary during the data analysis process, the reasons for any change will be fully documented.

To describe the sample, a descriptive statistic will be performed analyzing the mean, standard deviation, minimum, maximum and percentages of the sociodemographic variables. In addition, it will be possible to look at the average of those included and excluded in order to justify the excluded people. In this way it will be possible to describe the sample and observe the homogeneity between groups.

Next, a univariate and bivariate statistical analysis will be performed. First of all, it will be assessed whether or not the study follows a normal distribution in each of the variables. This analysis will determine whether to use parametric or non-parametric tests in the analysis of results based on the "p" value.

Equality of variance will then be analyzed through the Levenne test and finally the results will be analyzed. There will be a pre- and post-intervention analysis between groups and intragroups with a three-month follow-up. We can also analyze possible correlations between variables.

Qualitative analysis:

Qualitative analysis is a non-linear, interactive and dynamic process. It will consist of different parts following Colaizzi’s 7-stage method (18). We will start by transcribing the interviews and familiarizing ourselves with the data, then coding those ideas that are related to the research question. The codes obtained will be grouped into subcategories that share common aspects and will be described and located in the phenomenon studied. Finally, these subcategories will be categorized by looking for general ideas and possible relationships. The analysis will be performed through the program Atlas.ti 8.0.

1. **ETHICAL ASPECTS**

Recommendations for Good Clinical Practice: This study is based on the recommendations of Good Clinical Practice, the Declaration of Helsinki of the World Medical Association (mentioned in the 64th General Assembly, Fortaleza, Brazil, October 2013) and the applicable legal regulations. Therefore, all the researchers involved will sign a certificate of having read and understood this statement. If necessary, an adverse event notification form will be included in the appendices. It is necessary to maintain a rigorous and continuous quality control, which can guarantee the accuracy and scientific rigor of the data obtained, maintaining the conditions of homogeneity during the process of collecting the information. If necessary, the creation of a logistics committee will allow the proper coordination of all study groups and work to contrast the scientific coordination, methodological advice and the quality of the information obtained.

Information to be provided to participants and type of consent to be requested in the study: The model information to be provided to participants and the type of informed consent to be requested will be specified in the annexes to this effect. The appendices will also include, if necessary, a waiver sheet to allow participants to leave the study at any time. All participants will be verbally informed during the process of inclusion in the study by one of the researchers and will be sent online the fact sheets with all the detailed aspects. Subsequently, they will be asked for informed consent. They will also be provided with the consent form on image and voice rights.

Confidentiality: the strictest rules of professional conduct and confidentiality must be maintained at all times, and compliance with Regulation 2016/679 of the European Parliament and of the Council of 27 April 2016 on the protection of individuals ( RGPD) and Organic Law 3/2018, of 5 December, on the Protection of Personal Data and the Guarantee of Digital Rights (LOPD-GDD). The participant's right to confidentiality is paramount. The identity of the participant in the study documents must be coded, and only authorized persons will have access to personally identifiable details in the event that the data verification procedures require the inspection of these details. Identifiable personal details must always be kept confidential and will only be accessed by the principal investigator, the promoter and the persons authorized by the principal investigator and the relevant Health Authorities. In relation to the phenomenological study, it will not be possible to encode the identity of the participants as during the transcription phase we will have the video of the participant. The person responsible for making the transcripts will at all times guarantee the confidentiality of the data and once the transcripts have been made the videos will be deleted.

We can see all these documents in the appendices.

1. **EXPECTED BENEFITS**

At the participant level, the GraMI protocol is expected to decrease the DMF and, as a result, improve the quality of life and reduce the associated psychological factors.

At the level of participating hospitals, it is expected that they will be able to know a standardized way of applying IMG in this profile of patients.

At the level of the research group, it is expected to make communications in conferences and publications on the protocol and the results obtained, as well as its dissemination and implementation. In addition, the aim is to advance the doctoral thesis and try to get funded projects to continue research in this field.

1. **POSSIBLE UNWANTED OR SIDE EFFECTS**

The intervention is not invasive, so no serious side effects are expected with the intervention.

1. **COMPENSATION OR INSURANCE FOR PARTICIPANTS**

There is no consideration or insurance for the participants. If they wish, evolution reports can be prepared, comparing the initial, final and follow-up status of each participant.

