A non-probabilistic sampling rate type will be used. It consists of first determining a number of subjects with certain characteristics (inclusion criteria), and then selecting the first individuals who possess these characteristics and agree to participate in the study.

As participants are recruited, an outside person will randomize them through sealed envelopes that they will assign to the control or intervention group. An external person will perform the randomization so as not to influence the assignment of the participants. During the study, the only people who will be blinded will be the evaluators so that they do not have an influence on the assessments made according to the group to which they belong. Due to the nature of the intervention, and given that the information sheet explains the characteristics of the interventions, there is no guarantee that the participants will not deduce which group they belong to. However, the therapists who will perform the intervention cannot be blinded either.

1. **PROCEDURE:**

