**Step 1: Design the application**

In order to be able to carry out the first two techniques of the GraMI protocol (laterality recognition and motor imagery) a mobile application is required. This application will be designed by a team of UVic-UCC engineers and will be available for all devices. It will only be used by the participants in the experimental / intervention group. If, at the end of the study, the hypothesis that the GraMI protocol is effective in reducing the PLP is verified, the participants in the control group will be given the opportunity to use the application to carry out the protocol. The estimated design time for the app is four months (November 2021-February 2022), which will include piloting to test its usability and accessibility. During its design, a gamified application will be developed to encourage the motivation and adherence of the participant and aspects will be defined that will help the principal investigator in the supervision and follow-up of the intervention. In addition, the following aspects will be taken into account:

- The principal researcher of the project will install the application on the mobile device of the participant during the first educational session. This will allow you to learn how it works and help you become familiar with the application. Upon entering the application, the participant must register with their full name, username and be asked for the level of amputation (top or bottom) and side (right or left).

- The application will have two image banks differentiated according to the level of amputation (upper or lower extremity). Depending on the selection previously made by the participant, only the image bank related to his / her amputation will appear.

- Once you have entered the application, you will receive a calendar with a 6-week duration of the intervention (3 weeks for the laterality recognition phase and 3 weeks for the motor image phase).

- Through lock screens you will only be able to access the technique and level of progression that touches you at each moment of the intervention. The activity to be performed will be activated each day and the previous activity will be blocked. In this way we can guarantee the intensity and frequency established by the protocol.

- Scheduled to provide a daily reminder notification. In addition, the principal researcher of the project will contact the participant by telephone to encourage continuity with the intervention.

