The researcher conducting the interview will be an external person who has not performed the intervention or randomization, so as not to influence the questions and answers. This person has theoretical sensitivity about PLP and mirror therapy and this will make it easier to delve deeper into the topics during the interviews and better understand the experience. Subsequently, two members of the research group will perform the transcripts and analysis of the results. The aim of this triangulation is to achieve the highest possible objectivity in the results. The interviews will be recorded in voice and video format in order to be able to make a transcript as optimal as possible and will help not to lose the facial and body expressions of the participant. Only the research group and the researcher who conducted the interviews will have access to the recorded material. Each participant will have previously signed the consent to the image and voice rights. Once the study is complete, the recordings will be deleted. Once the transcripts have been completed, they will be sent to each participant to corroborate the information. This process will also be performed after the analysis of the results. You can see the consent form and the interview template in the appendices.

1. **VARIABLES:**

The assessments will be carried out by two people outside the intervention and the phenomenological study. These people will be two physiotherapists with clinical experience in the field of neurorehabilitation and / or pain, trained in research methods, calibrated with each other in order to minimize bias and will be blinded by the assignment of the groups. An initial assessment, a post-intervention assessment (9 weeks) and a follow-up assessment (12 weeks post-intervention) will be performed. The assessments will be carried out in the homes of the participants, in person and will last approximately 25-30 minutes.

The variables to be studied are differentiated between sociodemographic variables, amputation characteristics, independent variables and dependent variables. The first assessment will be the one that will last longer as all the variables will be collected, but the second and third assessment will last approximately 30 minutes as only the dependent variables will be collected.

- **Socio-demographic variables**; gender, age, marital status, height, level of education, level of physical activity, pathological and traumatic history, drugs administered and dose.

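### Arm labels are not masked for the research group that analyses the trial of its own protocol; a sign-off on A/B-labelled data is a cheap, minor improvement

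*Protocol*

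**What the plan says.** **Who is blinded.** Types of sampling and randomization: "During the study, the only people who will be blinded will be the evaluators". The Variables section describes these evaluators: "The assessments will be carried out by two people outside the intervention and the phenomenological study". They are two physiotherapists who carry out the assessments, and analysis is not among their tasks.

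**Who analyses.** Statistical analysis, Quantitative analysis: the data are coded once collection ends and then "processed and analyzed by the members of the research group".

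**What is decided during analysis.** Each variable is first checked for normality: "This analysis will determine whether to use parametric or non-parametric tests in the analysis of results". Neither the normality test nor the comparison tests are named. Comparisons are planned between and within groups, with a three-month follow-up, and "We can also analyze possible correlations between variables". Departures are foreseen: the sentence opening "If a deviation from the intended method is considered necessary during the data analysis process" asks that the reasons be documented. The same section calls for intention to treat and also sets a minimum of 80% of sessions for the results.

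**What the group sees.** Of the app, Step 1 says: "It will only be used by the participants in the experimental / intervention group". Its database is open to the research group. Under Step 3, two members of the group transcribe and analyse interviews, which are held with experimental-arm participants only.

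**The concern.** The analysts can know each participant's arm while they settle the test, the form of the outcome, exclusions and deviations. They also have an interest in the answer: Expected benefits lists publications on the protocol, its dissemination and implementation, progress of the thesis and future funding. A choice made with the arms visible can lean towards GraMI without anyone intending it. Documenting a deviation records it, but does not show that it was chosen without sight of the result.

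This matters somewhat more here because other protections are thin. Therapists are unblinded, participants may deduce their group, and the pain, quality-of-life and depression scales are self-completed. Masking at the analysis stage is one of the few safeguards still available.

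**Working it through.** **1. Are the analysts masked?** The sampling section restricts blinding to the evaluators, the Variables section makes these two outside assessors, and the analysis section gives the analysis to the research group. Read together, the analysts fall outside the blinded set. This follows from stated text, not from silence.

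**2. Does anything else hide the arm?** Coding at the end of collection does not say so. Under Ethical aspects, coding protects participants' identity. The group also holds app records that exist for one arm only and interviews from that same arm. No section conceals allocation from the analyst.

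**3. Does the remedy touch the design figure?** No. The plan's 50 participants reproduce with d = 0.81, two-sided alpha 0.05 and power 0.80. The t-test calculation gives 24.92 per group, rounded up to 25, so 2 × 25 = 50, with power 0.801 at 25 per group. (The alpha of 0.5 and beta of 0.8 printed in the sample-size section do not give 50; that is a separate matter.) Relabelling arms changes neither sample size nor power.

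**4. Can the harm be expressed as a false-positive rate?** Checked by simulating trials with no true effect, 25 per arm, 20,000 runs per setting. The distributions are assumptions, since the protocol gives none. Simulation error near 5% is √(0.05 × 0.95 / 20,000) = 0.15 percentage points.

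| Analyst's behaviour | Assumed data | Rejects at p < 0.05 |
|---|---|---|
| Normality check (Shapiro-Wilk per arm), then t-test or Mann-Whitney as it dictates | normal / gamma / lognormal | 5.2% / 5.1% / 5.0% |
| Smaller p of t-test and Mann-Whitney | normal / gamma / lognormal | 5.8% / 6.3% / 6.9% |
| Smaller p of the two tests, post score | normal, baseline correlation 0.5 | 5.6% to 6.2% over repeat runs |
| Smaller p of t-test on post score or on change | as above | about 9% |
| Smallest p of both tests on post score and change | as above | 10.4% to 11.1% over repeat runs |

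The first row is the rule the protocol states, and it is close to nominal. The other rows describe picking the smallest p-value, which the protocol does not describe. Most of the excess in the last row comes from leaving post score versus change open, not from t-test versus Mann-Whitney.

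**5. Would A/B labels lower those rates?** Swapping the labels changes the sign of t but not its size. It turns the Mann-Whitney U into 25 × 25 − U = 625 − U, which is equally far from 312.5. Two-sided p-values are therefore unchanged. In the four-way setting, false positives favouring GraMI were 5.1% to 5.2% whether the analyst picked the smallest p under masked labels or saw the arms and picked only favourable results. One fixed two-sided test allows 5% / 2 = 2.5% in that direction. The excess comes from leaving the choice open, so fixing the choice before comparing the arms is what removes it.

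**6. Can the 80%-session rule be applied under masking?** No. Only the GraMI arm has protocol sessions; controls receive an educational session, continue usual treatment and keep a diary (Step 2). For the first two phases the app log is the record of completion. Using that log, or forming the 80% set, reveals which label is GraMI.

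**The case against.** The strongest reply is that the protocol does not leave the test to taste: normality is checked first and the check determines the type of test. Followed as written, this keeps the error near 5%, and deviations must be justified. The exact tests and the form of the outcome are ordinary content of a statistical analysis plan, which may exist and is not shown here. Masking alone would not stop someone searching for a small p-value, and it is not wholly free, because a group that handles the app data and interviews may struggle to supply an analyst who has seen neither.

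Most of this stands. A reader might infer that unblinded analysis raises the false-positive rate to about 6% or 11%. The documents do not support that: the figures come from selecting the smallest p-value, they are the same under masked labels, and the protocol states a rule rather than such a selection. A reader might also infer that A/B labels would by themselves remove the risk at no cost. They would not; the sign-off before any comparison does most of the work.

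The reply does not remove the point itself. The protocol states who is blinded and who analyses, and the analysts are not blinded. Its normality rule leaves the normality test and comparison tests unnamed, and deviations remain open during analysis. If an unseen analysis plan does mask the analyst, the protocol's statement that only evaluators are blinded needs to be reconciled with it.

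**Conclusion.** The point holds as a minor one. By the protocol's own wording, the group that developed GraMI analyses the outcomes with allocation visible and with some decisions still open. What masking protects against is direction-dependent judgement: excluding data or adopting a deviation because of which arm it helps. The documents give no basis for putting a size on that, and none is claimed.

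This conclusion assumes that the word only in the blinding sentence means what it says, and that coding the data refers to data handling and identity rather than to hiding the arm. It does not assume any misconduct. Label: cheap improvement, not a threat to the validity of the trial.

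**What to change.** In Statistical analysis, Quantitative analysis, state that:

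1. The outside person who randomises supplies the outcome dataset under new study codes, with arms labelled A and B and with no app or interview data.
2. Before running any between-arm comparison, the analyst decides, dates and signs the outcome form (post score or change), the test, any data exclusions and any deviation.
3. The primary intention-to-treat analysis is then run, and the code is broken only after that.
4. The 80%-session rule is applied after unmasking, as a secondary analysis.

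Amend the blinding sentence under Types of sampling and randomization to match.

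**Cost.** A recoded dataset and a dated sign-off; no extra participants or visits, and no change to the sample size of 50 or its power. **Limit.** If the analyst also handles app or interview data, masking is only partial, and protection then rests mainly on the sign-off. Naming an analyst who handles neither avoids this but may require another person.

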**Removal**:

- Changes in medications that directly affect the main variable pain.

- Changes in the use or not of prostheses during the intervention.

Currently, the main line of treatment is pharmacological. As a result, most participants will receive medical treatment. So that this is not a condition in analyzing the effectiveness of our intervention, it will be analyzed that the participants are pharmacologically stable. By pharmacologically stable we mean that during the intervention there can be no changes in the drug that directly influences the PLP. There may also be no modifications to medications prescribed for other aspects but which may condition the PLP. An example of the latter would be antidepressants, which are adjuncts to the medications provided by PLP. If there are changes in medication that do not affect the pain, the intervention will be continued.

Prior to the intervention, the participants must have the established dose of medication, usually this dose is administered gradually until stability is achieved. Therefore, medication will be one of the variables to be collected to analyze and monitor this stability.

On the other hand, the elimination criterion according to the usefulness of the prosthesis is based on the fact that if the participant is wearing prosthesis, he / she will use it during the whole intervention, and I live in reverse, since the prosthesis could be a conditioning factor to study the effectiveness of our intervention.

1. **PARTICIPANTS:**

Participants will be recruited through the reference health professional of different hospitals that have amputee units, including the Hospital de la Santa Creu de Vic, Hospital de Sant Jaume de Manlleu, Hospital Pere Virgili, Asepeyo Sant Cugat Catalonia (Spain), which will assess its eligibility according to the established inclusion criteria. Once identified, the possible participants will be notified to the principal researcher, who will contact them by telephone to offer them the opportunity to participate and send them, via online, the information sheet with the details of the study. Those who agree to participate must sign the informed consent form and be informed that they have a waiver form so that they can withdraw from the study at any time they wish. Participants will be able to start the intervention once they have been registered or are already at home.

1. **TYPES OF SAMPLING AND RANDOMIZATION:**

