**Step 2: RCT**

The RCT description was performed following the *Templeate for Intervention Description and Replication (TiDier)* guide 26 in order to adequately describe all aspects of the intervention and promote study replication.

The duration of the intervention, both in the control group and in the intervention group, will be 9 weeks plus 12 weeks of follow-up. The estimated start date for recruitment will be March 2022 and will run until March-April 2023.

Both the participants in the control group and the intervention group will initially receive an educational session, in person or online, on the physiology of PLP, brain plasticity and the importance of rehabilitation. It will last approximately 30 minutes where they will be explained in detail that after an amputation there is an incongruity of visual, sensitive and motor information and maladaptive plasticity due to adjacent areas occupying the areas injured by the amputation. . This educational session will be given by the principal investigator of the project, who has clinical experience, teaching and research in the field of neurorehabilitation and pain.

Control group intervention:

After the educational session, the participant will continue with the conventional treatment he / she is receiving at that time. Participants will be provided with a follow-up diary in which they will have to record their activities, specifying the nature, frequency and duration of each activity.

At the end of the study, if the hypothesis that the GraMI protocol is effective in reducing the PLP is verified, the option will be given to the participants in the control group who can perform the intervention.

Intervention / experimental group intervention:

Participants in the intervention group will receive conventional treatment plus the GraMI protocol. If they do not receive conventional treatment, they will only perform the GraMI protocol.

GraMI protocol:

Education:

At the beginning of each of the three phases, there will be an educational session of approximately 30 minutes. During each of the sessions, online or in person, the purpose of the phase in which it is located will be explained, the procedure to be followed, common objectives will be established for each phase and the normal parameters to which must be reached in the laterality recognition phase:

- Accuracy of more than 80% of accurate images.
- Average image recognition speed.

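### The protocol labels the analysis intent to treat but does not say that people who stop, are removed or change treatment are still assessed at weeks 9 and 21

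*Protocol*

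**What the plan says.** Five parts of the protocol bear on this point.

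- **Analysis rule** (Statistical Analysis, Quantitative analysis). For "participants who have not completed the study due to dropout, have not fully completed treatment, or have even changed treatment", the protocol says that "any data that may have been collected will be analyzed for intent to treat".
- **Adherence threshold** (the next sentence). "The minimum number of sessions to be considered for the results will be 80" per cent. The protocol does not say whether this defines a separate analysis set or limits the main one.
- **Removal** (list after the exclusion criteria). Two triggers: "Changes in medications that directly affect the main variable pain" and "Changes in the use or not of prostheses during the intervention". The protocol does not say whether removal means leaving the intervention, the assessments or the analysis.
- **Withdrawal** (Participants). People are told "they have a waiver form so that they can withdraw from the study at any time they wish".
- **Assessments** (Variables). "An initial assessment, a post-intervention assessment (9 weeks) and a follow-up assessment (12 weeks post-intervention) will be performed". Procedure, Step 2 adds that in both groups the duration "will be 9 weeks plus 12 weeks of follow-up", which puts the visits at week 9 and week 21.

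The analysis described is a pre/post comparison between and within groups, using parametric or non-parametric tests.

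**The concern.** An intent-to-treat comparison needs an outcome from the people who did not follow the assigned course, not only a label. Here the label rests on whatever data happen to exist. There is no outcome measurement between baseline and week 9, so for someone who stops in week 3 everything depends on whether the week-9 home visit still takes place. The protocol leaves this open.

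If that visit is not made, the person has a baseline score only and cannot enter a pre/post test. Those left in the comparison are no longer the groups formed by randomisation, and the phantom limb pain result would be reported as intent to treat when it is not.

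This cannot be left to a statistical analysis plan. Such a plan can choose how to handle missing scores, but it cannot recover scores that were never collected.

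**Working it through.** **1. What exists for a person who leaves the intervention early**

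| Situation | Scores guaranteed by the text | Enters the week-9 pre/post test? |
| --- | --- | --- |
| Completes | baseline, week 9, week 21 | yes |
| Stops GraMI, stays in study | baseline; later visits neither promised nor excluded | unclear |
| Removed (medication or prosthesis change) | baseline; later visits not mentioned | unclear |
| Leaves the study before week 9 | baseline | no |
| Leaves the study after week 9 | baseline, week 9 | yes; lost only at week 21 |

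The app's records before week 9 (completion, hits, reaction speed) do not fill the gap. They are not dependent variables and exist only in the GraMI arm.

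**2. What the 80% sentence would do if applied to the main analysis**

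Scheduled sessions (Procedure, Step 2): phase 1, 2 × 5 × 3 = 30; phase 2, 2 × 5 × 3 = 30; phase 3, 1 × 5 × 3 = 15. The total is 75, and 80% of 75 is 60. Anyone who stops before the end of week 6 is below 60. Controls have no GraMI sessions to count, so the rule would select in one arm only.

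**3. The plan's own sample size**

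The sample-size section gives an effect size of 0.81 and 25 per group. A two-sample t-test at two-sided alpha 0.05 and power 0.80 needs 24.92, so 25 per group and 50 in total. (The printed alpha of 0.5 and beta of 0.8 have to be read in that way to reach 50.) The figure contains no allowance for loss. With 10%, 20% or 30% of each arm unassessed at week 9, 22.5, 20 or 17.5 per arm remain, and power at 0.81 falls from 80% to about 76%, 70% or 64%.

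**4. Illustration of bias (assumed values)**

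Let s be the share of an arm not assessed and g the amount, in SD, by which those lost do worse than those who stay. The arm's stayers then look better than the whole arm by s × g, so the between-group bias towards GraMI is

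s(GraMI) × g(GraMI) − s(control) × g(control).

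*Case A.* GraMI stayers gain 0.81, stoppers gain nothing, no stopper is assessed, no control is lost. Effect in all randomised = 0.81 × (1 − s).

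| s | Effect in all randomised | Effect shown | Overstatement, 1/(1 − s) − 1 |
| --- | --- | --- | --- |
| 10% | 0.81 × 0.90 = 0.73 | 0.81 | 11% |
| 20% | 0.81 × 0.80 = 0.65 | 0.81 | 25% |
| 30% | 0.81 × 0.70 = 0.57 | 0.81 | 43% |

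*Case B.* No true effect, loss in the GraMI arm only. With standard error √(1/n₁ + 1/25) and n₁ = 25(1 − s):

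| s | Bias, g = 0.5 | Type I error | Bias, g = 1 | Type I error |
| --- | --- | --- | --- | --- |
| 10% | 0.05 SD | 5.3% | 0.10 SD | 6.4% |
| 20% | 0.10 SD | 6.3% | 0.20 SD | 10.2% |
| 30% | 0.15 SD | 7.7% | 0.30 SD | 16.1% |

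*Case C.* Equal s and equal g in both arms: the two terms cancel. Bias is zero and only the power loss in step 3 remains. If controls who do badly leave more often, the sign reverses.

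**The case against.** The strongest reply is that the protocol never says early stoppers go unassessed. It lists dropout and incomplete treatment as separate cases, keeps both under intent to treat, and sets the home visit at 9 weeks with no adherence condition. A site could follow the text and visit everyone. This stands: a reader might infer that someone who stops in week 3 is bound to have a baseline score alone, and the text does not say so. The defect is that the visit is not secured.

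Three other stronger readings also fail.

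- *Withdrawal from the study is the only way out.* The Removal list is a second route. It adds to the concern, because follow-up after removal is not mentioned either.
- *The follow-up visit floats with each person's stopping date.* The 9-plus-12-week duration stated for both groups in Step 2 largely settles it at week 21.
- *The bias must favour GraMI.* The protocol does foresee pain during imagery and mirror therapy, so more stopping in that arm is plausible. But controls must keep a diary, may deduce their allocation, and are offered GraMI only at the end and only if it proves effective. Loss among controls is plausible too.

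It is also fair to say that handling the missing scores of those who truly withdraw may belong to a statistical analysis plan that is not at hand. The withdrawal form is in appendices that are not shown, so its options cannot be judged.

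**Conclusion.** The point holds as a gap in data collection beneath a stated intent-to-treat analysis. Nothing in the protocol keeps people who stop GraMI, are removed or change treatment on the assessment schedule. Anyone not visited at week 9 leaves the pre/post comparison, and the Removal criteria and the 80% sentence, as worded, can push it further towards completers. These sections need to be reconciled with the intent-to-treat sentence.

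Neither the size nor the direction of the bias is established, because the document gives no dropout rate. The overstatements of 11%, 25% and 43% should not be read as predictions. They require that stoppers gain nothing, that none of them is assessed and that no control is lost. Under milder assumptions (leavers 0.5 SD worse, GraMI arm only) the bias is 0.05 to 0.15 SD; with similar loss in both arms it can be nil. The repair is worthwhile because it is cheap and cannot be made after the visits have been missed.

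**What to change.** Amend the Removal and Participants sections and the Quantitative analysis section as follows.

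1. Separate two events: stopping or being removed from the intervention, and withdrawing consent to further assessment. The removal criteria themselves need not change for this purpose; what must be stated is that removal from the intervention does not end assessment. Check that the withdrawal form makes the same distinction.
2. State that every randomised participant who has not withdrawn consent to assessment is assessed at week 9 and week 21, counted from the start of the 9-week period, in both arms, whatever their adherence, removal or treatment change.
3. State that these scores enter the intent-to-treat comparison in the group to which the person was randomised.
4. Limit the 80%-of-sessions rule to a separate per-protocol analysis.

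The cost is protocol wording plus home visits to people who have stopped, all of which are already planned for every participant. The estimated effect may come out smaller, because people who did not complete GraMI would count in it.
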